**Consent and Baseline Blood Sample**

All volunteers responding positively following the period of consideration will be invited to the HNU for a blood sample. On arrival at the HNU, the study scientist will go through the consent form with the volunteer (annex 3) and encourage any questions they may have at this stage; after which the volunteer will sign the consent form agreeing to participate in the study. Copies of the consent form will be kept in the study records, the patient hospital notes and a copy given to the volunteer to keep. GPs will be informed by letter (annex 4) of their patients’ participation in the study.

A Research Nurse at the HNU, IFR will complete a basic health questionnaire with the volunteer. This includes measurements of blood pressure, height and weight, BMI and a medication declaration form agreeing to inform the study scientist of any medication they may have to take (annex 5). Volunteers will be excluded if they are found to have depressed or elevated blood pressure (<90/50 or >160/100) or BMI <18.5 or >35. A 10ml (2 teaspoons) blood sample will be taken by venepuncture by a qualified Research Nurse. This blood sample will be required in order to extract DNA from whole blood to determine genotypes for GSTM1, GSTT1 and GSTPi genes.

Once recruited onto the study, volunteers will be assigned a code, only the study scientists approved by the Ethics Committee being able to link codes to volunteers. Samples to be used for determining GST genotypes will be double encrypted so that individuals cannot be linked to the resulting genotype. All personal information will be kept confidential and known only to the Chief and Principle Investigators, HNU Research Nurses and Medical Advisor and the volunteer’s GP.

**Dietary Assessment**

We wish to measure habitual diet in both groups since the control group may consume a high amount of cruciferous vegetables as part of their normal diet. We also want to investigate confounding factors of other nutrient groups such as energy intake and dietary fibre in relation to baseline gene expression. This will be measured using the IFR standard 7-day food diary of estimated intake (annex 6). Volunteers will be asked to include use of any dietary supplements or herbal treatments in the diary.

Volunteers will be instructed to record their intake of food, beverages and supplements consumed over a 7-day period (incorporating 7 different days, including weekends) using household measures as an indication of portion size. Details of how to complete the diary are given in annex 6 along with an example diary. Halfway through and towards the end of the 12-month dietary intervention, 7-day food intake diaries will again be completed. The food intake diaries will be analysed using ‘Diet Cruncher’ and UK food composition tables.

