**STUDY DESIGN**

The study will be led by [name] and [name] at the Institute of Food Research, Norwich, in collaboration with [name] and [name] at the Urology and Histopathology departments of the Norfolk and Norwich University Hospital (NNUH) NHS Trust. A flow chart of the overall study is given in figure 1.

This is a parallel, dietary intervention studying male patients with high-grade PIN. Patients will be matched by genotype and diet into two dietary groups: (i) consuming 400g ITC-enriched broccoli per week (n=20) or (ii) consuming 400g peas per week (n=20). The study will involve dietary monitoring and collection of blood, urine and prostatic biopsy samples in a 12-month dietary intervention period. The prostate biopsies and blood will be collected during routine endoscopies as part of normal diagnostic procedure for this group of patients. The urine samples will be additional to routine procedure. It is anticipated that the drop out rate for this study will be 40% due to the progression of high-grade PIN to prostate cancer within the 12-month study period.

*Figure 1. Study Design.*

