**Recruitment Policy**

Patients with high-grade PIN, aged 30-70 years will be identified and recruited by [name], consultant urologist at the NNUH. Following a verbal expression of interest in the study, [name] will send a letter (annex 1) with a volunteer information sheet (annex 2) inviting potential volunteers to take part in the study. Volunteers will return a reply slip to IFR, contact details of the study scientist ([name]) will be provided to all potential volunteers.

Volunteers will be matched by genotype into two dietary groups: (i) consuming 400g ITC-enriched broccoli per week (n=20) or (ii) consuming 400g peas per week (n=20). Volunteer recruitment will continue until a total of 40 men have completed the trial. It is envisaged that 17 patients will be recruited per group and that the drop out rate for this study will be 40% due to the progression from high-grade PIN to prostate cancer within the 12-month study period. Interested volunteers will be invited to an information exchange at the Human Nutrition Unit (HNU) at IFR where the study scientist will explain details of the trial and encourage the volunteers to ask any questions. During this consideration period the volunteers will not be contacted.

*Inclusion criteria:*

- Male
- Diagnosed with high-grade PIN
- Aged between 30 and 70 years
- Smokers and non-smokers

*Exclusion criteria:*

- Undergoing chemopreventative therapy
- Receiving testosterone replacement medicines
- Prescribed 5 reductase inhibiters
- Active infection requiring treatment
- BMI <18.5 or >35
- Unable to give informed consent to take part
- Diagnosed with diabetes

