**Dietary Intervention**

After giving fully informed, written consent, the volunteers will be matched by genotype and cruciferous vegetable consumption. The diet diary will be used to define high (> 3 portions per week) or low (< 1 portion a week) habitual consumers of cruciferous vegetables. Volunteers will be divided into two dietary intervention groups accordingly.

1. The ‘peas’ group will be asked to consume an additional 4 portions (100g each) of peas per week as part of their normal diet.

2. The ‘broccoli’ group will be asked to consume an additional 4 portions (100g each) of a special variety of broccoli, selectively grown for its enhanced glucosinolate content, per week as part of their normal diet.

Volunteers will be asked to modify their diets for a total of 12 months. This is to enable us to detect any long-term changes in gene expression and to coincide with the routine TRUS examinations every 6 months. Volunteers can choose which day to eat the vegetables, but will be asked to keep a record of when the vegetables were eaten.

Should the volunteers wish to go on holiday during the 12-month period, they will not be expected to adhere to the intervention. We will ask the volunteers to inform us of their planned holiday dates so that we can keep a record. We will ask them to avoid booking holidays for more than four weeks at a time or two weeks either side of their visits to the clinic and not within a month of the final assessment.

*Supply of Vegetables*

The broccoli will be grown and harvested by Olga Ltd, Boston, Lincolnshire, and processed by Christian Salvesen, Bourne, Lincolnshire. The broccoli is a hybrid cultivar, conventionally crossed with a wild species that has an enhanced level of the glucosinolate called glucoraphanin (precursor of sulforaphane). Samples will be packaged into 100g portions and stored frozen at -18oC until cooked by the volunteer. Frozen peas will be bought from a supermarket. Both types of frozen vegetable will be delivered to the volunteers on a regular basis by a member of the study team or Polymek, a temperature controlled delivery service, at a time convenient to the volunteer. Should any volunteer not own a freezer, IFR will loan a PAT tested freezer to the volunteer for the duration of the study.

*Cooking Guidelines for Frozen Vegetables*

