**STATISTICAL ANALYSIS**

*Statistical Power*

It is not possible to calculate the power for differences in gene expression between the two intervention groups because to date there are no relevant publications that describe the effects of ITCs on gene expression *in vivo*. This is a pilot study designed to provide data from which to calculate power for future studies in this field. The nature of a power calculation is to obtain the probability of detecting a difference that is true as opposed to a false negative result. It is arguable as to the appropriateness of such calculations when applied to Affymetrix gene expression data because the number of genes is so large (>47,000). Therefore we are more concerned with controlling false positive results (type I error).

All array data will be analysed using a simple linear model comparing significant differences in gene expression between broccoli and pea treatment groups. Impact of genotype will also be included, combining regression analysis with analysis of group differences. Pair wise comparisons between time points (baseline, mid and end points) and treatment (broccoli or peas) will be made by dividing by signal intensity to give a fold induction for each gene. Advice will be sought from [name], Biostatistician at the Institute of Food Research, Norwich.

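### Habitual cruciferous intake helps form the groups but is absent from the stated linear model; this costs precision if intake is balanced and predictive, and risks bias if it is not balanced

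*Protocol*

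**What the plan says.** Dietary Assessment explains the purpose of the 7-day diary: habitual diet is measured in both arms because "the control group may consume a high amount of cruciferous vegetables as part of their normal diet". The diary is completed at baseline and twice more during the intervention.

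The protocol describes the formation of the groups in three places:

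- Study Design: "Patients will be matched by genotype and diet into two dietary groups".
- Dietary Intervention: "the volunteers will be matched by genotype and cruciferous vegetable consumption", with the diary used to "define high (> 3 portions per week) or low (< 1 portion a week) habitual consumers of cruciferous vegetables".
- Recruitment Policy: "Volunteers will be matched by genotype into two dietary groups". Diet is not mentioned here.

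Statistical Analysis commits all array data to a simple linear model comparing broccoli with peas and adds one further term: "Impact of genotype will also be included, combining regression analysis with analysis of group differences". It also plans pairwise fold changes between time points and treatments. Habitual cruciferous intake is not named in either analysis. Dietary Assessment gives other diet data (energy, fibre) a role in relation to baseline expression, but gives cruciferous intake no role in the arm comparison.

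**The concern.** Two factors shape the groups and only one appears in the model. The one left out measures background exposure to the compounds under study. The trial's hypothesis is that long-term broccoli consumption changes gene expression, so the sponsor cannot easily assume that long-term habitual intake is irrelevant to it.

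What is at stake depends on whether the matching works. If it balances intake, an unadjusted analysis is valid but wasteful, because it charges to random error a variance that the design has already removed from the arm difference. If it does not, an intake difference between arms enters the estimated diet effect. The same added term addresses both cases.

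**Working it through.** **Inputs from the protocol.** 20 per arm is the stated group size, with 40 completers in total. Recruitment Policy also gives 17 recruited per group with 40% dropout, which yields 17 × 0.6 = 10.2, so 10 per arm is checked as well. Genotype null frequency is taken as 40% (Background).

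**Assumed.** R², the share of outcome variance explained by habitual intake, is not given and is ranged from 0 to 0.30. Intake is treated as a two-level factor, half high and half low. Outcome SD is 1. The protocol states no power, effect size or SD, so there is no figure of its own to reproduce.

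**Case A: intake exactly balanced.** Let N be the total number of men. The stated model (intercept, treatment, genotype) has N − 3 residual degrees of freedom; adding intake leaves N − 4. With intake balanced across arms and genotype, the expected residual variances are:

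- stated model: (1 − R²) + N·R²/(N − 3)
- with intake added: 1 − R²

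The ratio of 95% interval widths, stated to adjusted, is approximately

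√{[(1 − R²) + N·R²/(N − 3)] / (1 − R²)} × t(N − 3)/t(N − 4).

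For N = 40 and R² = 0.20: (0.80 + 40 × 0.20/37)/0.80 = 1.0162/0.80 = 1.270, with square root 1.127. Multiplying by 2.0262/2.0281 gives 1.126.

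Simulation (20,000 runs per setting) agrees with the formula:

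| Assumed R² | Width ratio, 20 per arm | Width ratio, 10 per arm | True type I error of stated model at nominal 0.05, 20 per arm |
|---|---|---|---|
| 0 | 1.00 | 1.00 | 0.05 |
| 0.05 | 1.03 | 1.03 | 0.045 |
| 0.10 | 1.06 | 1.06 | 0.040 |
| 0.20 | 1.13 | 1.13 | 0.029 |
| 0.30 | 1.21 | 1.22 | 0.019 |

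The adjusted model stays at about 0.05 throughout. At R² = 0 the extra term costs essentially nothing.

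**Case B: intake not balanced.** The bias in the unadjusted arm difference is the intake coefficient times the difference in mean intake between arms. For a half-and-half factor (SD 0.5) the coefficient is √R²/0.5 = 2√R². As an assumed illustration, take 7 high consumers in one arm and 13 in the other, of 20 each. The mean difference is 6/20 = 0.3 and the bias is 0.6√R²:

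| Assumed R² | Bias (outcome SDs) | Type I error, stated model |
|---|---|---|
| 0.10 | 0.19 | 0.08 |
| 0.20 | 0.27 | 0.11 |
| 0.30 | 0.33 | 0.13 |

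With intake in the model, type I error returns to about 0.05, provided intake is measured without error and enters in the right form. A 7-day diary will meet that only in part.

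**Is balance secured?** Four features say it is not. Recruitment Policy omits diet from the matching. The high and low cuts (above 3, below 1) leave 1 to 3 portions a week unclassified. No random allocation is described. The expected 40% dropout can undo whatever balance existed at entry.

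**The case against.** The strongest reply is that Statistical Analysis is open text. It says genotype will also be included, not that genotype alone will be, it defers to a biostatistician, and a fuller covariate list may sit in an analysis plan that is not shown. Genotype also has its own reason to be there, since the third objective relates it to expression, so its presence does not prove a policy of adjusting for matching factors. This stands in part: the protocol is silent on intake and does not rule it out. But it does state a specific model for all array data, and naming a baseline factor already used to form the groups is a concrete improvement to that statement.

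A second reply is that the harm may be nil. Nothing in the protocol links habitual intake to expression. Comparisons between time points cancel a stable additive effect, and the 48-hour cruciferous exclusion before clinic visits limits acute effects. This also stands, and is why zero belongs in the range. It does not dispose of the point: the linear model is worded for expression rather than change, and the exclusion does not remove chronic exposure.

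A third reply is that a conservative test suits a pilot more concerned with false positives. That is fair under Case A but not under Case B.

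Two stronger readings are tempting and unsupported. A reader might infer that the covariate would separate background exposure from the diet effect. It would not: if pea-arm men eat many cruciferous vegetables the contrast is diluted, and a baseline main effect does not cure dilution. A reader might also weigh habitual portions against the enriched portions using the stated 3-4 fold increase. That figure compares enriched with standard supermarket broccoli only, and the protocol gives no equivalence for other cruciferous vegetables.

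**Conclusion.** The point holds in conditional form. Habitual cruciferous intake is measured at baseline and is a matching factor in two of three descriptions, yet it is missing from the stated model. If intake is balanced and predictive, intervals are about 3 to 6% too wide at an assumed R² of 0.05 to 0.10, 13% at 0.20 and 21% at 0.30, and not too wide at all at 0. If balance fails, the omission can bias the arm comparison, and the protocol does not secure balance. It would be wrong to say outright that the error bars are too wide, because R² is unknown and the direction of the harm depends on how the matching turns out. The case for the change rests on its low cost and on its covering both possibilities.

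**What to change.** In Statistical Analysis, add baseline habitual cruciferous intake from the first diary to the linear model beside genotype, as continuous portions per week so that men at 1 to 3 portions are included; or state why it is left out. Reconcile Study Design, Recruitment Policy and Dietary Intervention on whether diet is a matching factor. Use only the baseline diary for this term. Total intake from the later diaries is measured after allocation and, once the study broccoli is counted, is nearly determined by arm, so adjusting for it would replace the arm contrast rather than sharpen it.

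The cost is one degree of freedom and a sentence or two of text. No new data are needed.

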**Compliance**

Volunteers will be asked to fill in a dietary record sheet during the 12-month intervention period, recording a tick each time they eat their vegetable portion (annex 7). This is intended to aid compliance of the dietary interventions and also to be used in comparison with the 7-day diet diary. Volunteers will be telephoned fortnightly by a member of the study team to monitor progress and the vegetable record sheet will be collected from the volunteer by a member of the study team to coincide with the delivery of frozen vegetables.

**Sample Collection**

Biopsy samples will be collected from the NNUH tissue bank and taken to IFR for analysis. Blood samples for PSA will be taken at the Urology clinic prior to the TRUS examination. Urine samples will be collected at the Urology clinic by a study scientist. Blood samples for genotyping will be collected at HNU. The plan for sample collection is detailed in figure 2.

*Blood Samples*

A 10ml blood sample will be collected at baseline for DNA extraction to determine genotype. DNA will be extracted at IFR. Further 5ml blood samples will be collected by venepuncture during the visits to the Urology Clinic (mid-way and post intervention) by a qualified nurse or phlebotomist. The samples will be analysed in the Biochemistry department at the NNUH for prostate specific antigen levels (PSA).

*Urine Samples*

At the mid-way time point, one 24 hour urine collection will be required from volunteers in each group following consumption of one of their vegetable meals. Volunteers will be provided with a labelled container (plus 1g ascorbic acid as a stabilising agent) in which to collect urine. They will be required to collect total urine volume immediately after consumption of a meal containing the peas or broccoli for 24 hours. The containers of urine will be collected by a study scientist at the urology clinic at the 6 month time point.

This 24 hour urine sample will provide qualitative evidence that the volunteers are receiving systemic exposure to ITCs because from previous investigations we know that if ITCs are present in the urine, they must also have been present in the plasma. Furthermore, this will provide useful information about the relative range of ITC excretion, absorption and metabolism in each of the volunteers. This will be vital for interpretation of the gene expression data. In addition the urine analysis will also confirm that the volunteers are cooking the broccoli correctly.

*Prostatic Biopsy Samples*

Volunteers will be asked to exclude cruciferous vegetables from their diet 48 hours prior to each visit to the clinic to avoid acute effects. The types of vegetables to avoid will be indicated in the dietary diaries. Biopsies of the prostate will be taken before, during and after the 12-month dietary intervention. The collection of all biopsy samples will occur at the urology clinic at the NNUH during routine Trans Rectal Ultrasound (TRUS) guided endoscopies. Thus, the samples required for the study will be collected at the same time as samples required as part of normal medical care. All patients will receive an explanation of the TRUS procedure by their consultant prior to the examination and a standard information sheet (annex 8).

The consultant will examine the prostate with an ultrasound probe. This is inserted into the rectum and images on a screen guide the sampling needles into the prostate. A small amount of tissue (10-20mg) is removed from the gland with the needles. The procedure takes approximately 30 minutes. As part of normal clinical care eight prostatic biopsy samples are collected for histology, in addition, up to six biopsy samples will be collected for the broccoli, peas and PIN study. The consultant will note from which lobe (right or left) the samples were taken.

Samples will be immersed in RNA later at the point of collection and subsequently snap frozen in liquid nitrogen before being transported to the tissue bank at the NNUH. A member of the study team will collect the samples from the tissue bank and transport to IFR for analysis. Tissue bank information sheets will be read (annex 10) and tissue bank consent forms (annex 9) signed by all volunteers prior to the TRUS procedure and copies will accompany all tissue transported to IFR.

*Progression to Prostate Cancer*

It is estimated that 30-40% of the study population may develop prostate cancer during the 12-month intervention. Volunteers diagnosed with cancer will be given appropriate medical counselling and advised to withdraw from the study by letter (annex 11). All non-medical members of the study team will be guided by the clinicians as to the most appropriate course of action for these individuals.

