Prostate biopsy tissue will be taken before and after intervention of either broccoli or peas. We are primarily interested in the effect of broccoli on gene expression. However, peas are a good control because they cause the same change to the volunteers’ dietary regimen as adding broccoli and because they contain negligible amounts of glucosinolates. There is epidemiological evidence that peas may also be beneficial in reducing prostate cancer risk, but by different pathways to SF mediated action, Key *et al* (1997).

The study will use changes in gene expression as the main biomarker of effect. RNA will be extracted from the tissue and hybridised onto Affymetrix arrays. We will use validated software to create a gene expression profile of functional clusters of genes that are perturbed by the broccoli intervention. Subsequent analysis of selected genes by RT-PCR will confirm any significant changes in gene expression.

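### The 48-hour exclusion before each biopsy covers the broccoli arm's study vegetable but not the pea arm's, and the month-6 urine test meal is not reconciled with it

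*Protocol*

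**What the plan says.** **Exclusion.** Under Sample Collection (Prostatic Biopsy Samples) the protocol says: "Volunteers will be asked to exclude cruciferous vegetables from their diet 48 hours prior to each visit to the clinic to avoid acute effects". It adds: "The types of vegetables to avoid will be indicated in the dietary diaries". The same section sets the biopsy schedule: "Biopsies of the prostate will be taken before, during and after the 12-month dietary intervention".

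**Eating days.** Dietary Intervention asks each arm for four 100 g portions a week of its vegetable and leaves the timing open: "Volunteers can choose which day to eat the vegetables". It asks men to record when portions are eaten and gives the detection of long-term expression changes as one reason for the 12-month period. Nothing in the protocol restricts peas before a visit.

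**Urine.** Sample Collection (Urine Samples) plans one 24-hour collection per man in both arms, mid-way through the intervention: "They will be required to collect total urine volume immediately after consumption of a meal containing the peas or broccoli for 24 hours". Hand-over is fixed: "The containers of urine will be collected by a study scientist at the urology clinic at the 6 month time point". Figure 2 lists biopsies, blood and urine together under the second sample collection.

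**Control and comparison.** The Background section explains that peas were chosen partly because their glucosinolate content is negligible. It also grants: "There is epidemiological evidence that peas may also be beneficial in reducing prostate cancer risk", through pathways other than those of sulforaphane. Statistical Analysis compares expression between the two arms and between time points, on arrays of more than 47,000 transcripts (Sample Analysis).

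**The concern.** The exclusion separates lasting change from the short-term response to a recent meal. It does so for one arm's study vegetable only. If peas have any acute effect on prostate expression, that effect can be present in pea-arm biopsies at months 6 and 12, while the corresponding broccoli effect has been given 48 hours to fade. The between-arm contrast, and the pea arm's change from baseline, would then mix acute with chronic effects.

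The month-6 urine meal raises a second, narrower issue. A man who finishes his collection as he leaves for the clinic has eaten broccoli inside the window that the exclusion is meant to keep clear. If some men do this and others do not, acute ITC exposure at the month-6 biopsy is uneven within the broccoli arm, and it differs from month 12, where no urine meal is planned.

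**Working it through.** The protocol gives no figure to reproduce here. It declines a power calculation and states no effect size or variance. The check compares the instructions and does the timeline arithmetic.

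**1. Last permitted study portion before biopsy**

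| Visit | Broccoli arm | Pea arm |
|---|---|---|
| Baseline | none (before allocation) | none (before allocation) |
| Month 6 | at least 48 h by the rule; see step 3 for the urine meal | from 0 h |
| Month 12 | at least 48 h | from 0 h |

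The asymmetry is possible at both post-baseline visits. For ITCs there is none from the rule itself, because both arms avoid cruciferous vegetables and peas supply almost no glucosinolate.

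**2. How often could a pea portion fall in the last two days?** The protocol does not say how men space their four weekly portions. As an illustration, assume that eating days fall at random within the week.

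- Four portions on four different days: 1 − C(5,4)/C(7,4) = 1 − 5/35 = 86%.
- Two portions on each of two days: 1 − C(5,2)/C(7,2) = 1 − 10/21 = 52%.
- All four on one day: 2/7 = 29%.

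Under these assumptions recent pea exposure at biopsy ranges from about three men in ten to more than eight in ten. The rule sets it to zero for broccoli.

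**3. Urine meal at month 6.** Let the meal be M hours before the visit. Collection ends M − 24 hours before the visit, and the exclusion is respected in the broccoli arm only if M ≥ 48.

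- M = 24: collection ends at hand-over; broccoli was eaten 24 h inside the 48 h window.
- 24 < M < 48: the exclusion is still broken.
- M = 48: both instructions are met; the finished container is kept 48 − 24 = 24 h.
- M = 72: both are met; the container is kept 48 h.

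The protocol does not state M, and it does not exempt the test meal from the exclusion.

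**4. Share of arrays open to the urine problem.** Inputs: 20 men per arm (Study Design) and two arrays per man per visit (Sample Analysis, Biopsy Samples).

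- All post-baseline arrays: 2 arms × 20 × 2 arrays × 2 visits = 160.
- Broccoli arm at month 6: 20 × 2 = 40.
- Share: 40/160 = 25%.

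With equal arms and a fraction r of month-6 men still present at month 12, the share is 1/[2(1 + r)]. That is 25% at r = 1. If the whole of the protocol's anticipated 40% drop-out fell between the two visits (r = 0.6), it would be 1/3.2 = 31%. Both are upper limits, reached only if every broccoli-arm man ate the test meal inside the window.

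**The case against.** The best defence of the rule is that it targets the exposure under study. It removes foods that deliver ITCs, it binds both arms, and the control vegetable delivers almost none. The only stated reason to think peas active is epidemiological evidence on cancer risk, which says nothing about prostate expression within 48 hours of a meal. This stands as a limit on the size of the problem. It does not remove the asymmetry, because the planned comparison is not confined to ITC-responsive genes and the protocol itself allows that peas may act by other routes.

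On the urine, a reader might infer that the two instructions contradict each other. They do not: a meal at least 48 hours before the visit satisfies both, and the exclusion carries no exception. Nor is harm shown from keeping the container, since ascorbic acid is supplied as a stabiliser and no storage limit is given that a 24-hour hold would break. What remains is that nothing rules out a collection timed to end at hand-over.

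Volunteer instructions also sit in annexes that are not shown and may give the meal timing. The food list in the diary could do so too, but the body text limits the exclusion to cruciferous vegetables.

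Finally, eating records are already planned under Compliance and Dietary Intervention, so late portions could be identified at least to the day. That helps description. With about 20 men per arm it would not reliably separate acute from chronic effects afterwards.

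**Conclusion.** The point holds in a limited form. As written, the exclusion controls recent intake of the allocated vegetable in one arm and not in the other at both post-baseline biopsies, so recent exposure can differ by arm in the main comparison. The size of any resulting expression difference cannot be derived from the protocol. The frequencies of 29% to 86% rest on an assumed random spacing of portions.

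The urine meal is an unreconciled timing gap. It can affect at most the broccoli arm's month-6 arrays: about 25% of post-baseline arrays with equal arms and full retention, or 31% in the drop-out case above. Month 12 is untouched by it.

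Two stronger inferences are tempting and not supported. One is that acute exposure does differ by arm: the text permits this but does not make it certain, since a pea-arm man may happen to eat no peas before his visit, and ITC exposure differs from what the rule intends only if the test meal falls inside the window. The other is that half of the post-baseline arrays are exposed to the urine problem: that counts pea-arm arrays, which a broccoli test meal cannot affect.

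**What to change.** - **Exclusion.** Word the pre-visit exclusion, at whatever length the investigators retain, so that it covers the allocated study vegetable in both arms as well as cruciferous vegetables generally.
- **Urine meal.** Reconcile the Urine Samples and Prostatic Biopsy Samples text by stating the interval between test meal and clinic visit, so that the meal lies outside the pre-biopsy window. One way is to do the collection in another week around month 6, with the container picked up at a planned vegetable delivery. If hand-over at the clinic is kept, state how the finished container is to be stored until then.
- **Data.** Use the portion records already planned to derive time since last study portion at each biopsy, and report it by arm and visit.

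The cost is a change to the instruction sheets. Pea-arm men must time portions around their visits, and urine pick-up moves to a contact that already exists. No extra visit or sample is needed.
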